## Abstract

**Background:**

There are many comorbidities associated with Down syndrome (DS), including obstructive sleep apnea (OSA) and masticatory muscle alteration. Muscular hypotonia, in particular, of the masticatory and oropharyngeal muscles is one of the main characteristics of individuals with DS, resulting in impairments of speech, swallowing, and mastication in these individuals. In addition, total or partial obstruction of the airways during sleep can occur due to pharyngeal hypotonia, leading to snoring and to OSA. This progressive respiratory disorder is associated with a high risk of morbidity and mortality in individuals with DS. The aim of this research is to assess the therapeutic effects of surface neuromuscular electrical stimulation (NMES), the mastication apparatus (MA), and a mandibular advancement oral appliance (OA_m_) with an embedded thermosensitive microchip on the functions of masticatory muscles (bilateral masseter and temporal muscles), physiological sleep variables, and salivary parameters in adult patients with DS.

**Methods:**

The patients with DS will be randomly selected and divided into three groups (DS-NMES, DS-MA, and DS-OA_m_) with a minimum of 10 patients in each group. A thermosensitive microchip will be embedded in the OA_m_ to record its compliance. The therapeutic effects on masticatory muscle function will be investigated through electromyography, a caliper, and a force-transducer device; the sleep variables, in turn, will be evaluated by means of polysomnography. The physicochemical and microbiological properties of the saliva will also be analyzed, including the salivary flow, viscosity, buffer capacity, cortisol levels (susceptibility to psychological and/or physical stress), and *Pseudomonas aeruginosa* levels (risk of aspiration pneumonia) in these patients. The methods determined for this study will be carried out prior to and after 2 months of the recommended therapies.

**Discussion:**

The primary outcomes would be the improvement and/or reestablishment of the function of masticatory muscles and the physiological sleep variables in this target public since individuals with DS commonly present generalized muscular hypotonia and dysfunction of the oropharyngeal musculature. As a secondary outcome indicator, the impact of the applied therapies (NMES, MA, and OA_m_) on the salivary microbiological and physicochemical properties in DS individuals will also be assessed. Furthermore, the compliance of OA_m_ usage will be measured through a thermosensitive microchip.

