## Methods/design

This is a randomized, controlled, three-arm clinical trial conducted according to the ethical standards established in the 1961 Declaration of Helsinki (as revised in Hong Kong in 1989 and in Edinburgh, UK in 2000). This study was registered in the World Health Organization Universal Trial (UTN; number U1111-1201-3155) and Registro Brasileiro de Ensaios Clínicos (ReBEC; number RBR-3qp5np). It was also approved by the Brazilian Human Research Ethics Committee of the Institute of Science and Technology (CEPh 2.127.141; process number CAAE 64173616.4.0000.0077). All caregivers will be informed about the proposal therapies and will provide written informed consent. The whole study design (Fig. 1) and the SPIRIT checklist(aditional file 1) were followed. In addition, a SPIRIT figure is provided to illustrate the study schedule for the enrolment, interventions, and assessment (Fig. 2).

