### Sample size

Power analysis or Power test is the process used for determining the sample size for this study, using SPSS (version 22.0.0.0). This is based on a work entitled “Effects of Neuromuscular Electrical Stimulation on the Masticatory Muscles and Physiologic Sleep Variables in Adults with Cerebral Palsy: A Novel Therapeutic Approach” [15]. The intervention was considered to result in a minimum effect similar to the EMG activity of the masseter and temporalis muscles in disabled adults. Thus, the sample size obtained revealed that 90% reliability to identify a relevant outcome will be present at the bidirectional α level of 0.05 with 10 subjects deemed necessary in each group, to which five individuals will be added to compensate for possible dropouts. Due to the risk of withdrawal, 45 patients will be recruited.

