### Statistical analysis

Whenever applicable, the data will be presented as average ± standard deviation. The paired *t* test will be used in order to compare continuous variables with normal distribution, prior to and after polysomnography, as well as specific therapies. If the data show a non-normal distribution, then the Wilcoxon test will be used. The groups will be compared to one another using ANOVA or Mann–Whitney U test, according to the distribution. *P* ≤ 0.05 will be considered statistically significant. Missing data will be treated as worst-case scenario imputation. All analyses will be performed using SPSS 16.0.

All data will be stored on a notebook exclusively for this purpose, as well as on a hard disk for increased safety of data storage. Data will be allocated to a file with a number that corresponds to each participant and will be managed by the assistants, not available to the professionals who will carry out the interventions.

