## Discussion

This clinical trial will assess the physiologic sleep variables, masticatory function of the masseter and anterior temporalis bilateral muscles, and salivary parameters by means of PSG, sEMG, and specific salivary tests (cortisol levels, presence of *P. aeruginosa,* salivary flow, and pH) respectively, prior to and after mandibular advancement oral appliance (OA_m_), neuromuscular electrical stimulation (NMES), and mastication apparatus (MA) therapies in patients with Down syndrome. As the primary outcome, the authors believe that OA_m_, neuromuscular electrical stimulation, and mastication apparatus therapies may improve masticatory and oral pharynx muscle modulation, adjusting them to a level close to normality, which may lead to a balanced muscle activity contributing to reduce snoring/sleep apnea. Good sleep quality is likely to reduce corporal stress, as shown by the decrease in cortisol levels in the saliva, as a secondary outcome. In addition, the authors expect an improvement in other salivary parameters, as the absence of snoring and/or sleep apnea, which result from the act of breathing through their mouth, will contribute to the balance of the microorganisms in the oral cavity. Moreover, polysomnography will be used to evaluate the other sleep variables and the authors believe that sleep quality will improve after all therapies have been carried out. Another expected outcome is to measure the objective compliance and adherence to the OA_m_ with an embedded microsensor thermometer.

It is important to highlight that none of these therapies will cause any injuries to the participants, so the hypothesis of harm or of adverse side effects does not apply to the present study.

Neuromuscular electrical stimulation (NMES) may produce a feeling of discomfort due to the electrical stimulus applied on masticatory muscles; however, it does not offer foreseeable risks. The mastication apparatus (MA) does not produce discomfort or foreseeable risks. The mandibular advancement oral appliance (OA_m_) embedded with a thermosensitive microchip may initially produce discreet dental and muscular discomfort, with possible temporary hypersalivation and risks of occlusal changes. The polysomnography, surface electromyography, and specific salivary tests do not produce discomfort or foreseeable risks.

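### Two whole outcome domains are primary with no variable named, and every test uses P ≤ 0.05, so the two-sided 0.05 in the sample size is not the error rate of the primary conclusion

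*Protocol article*

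**What the plan says.** The Discussion paragraph of the Abstract defines success by domain: "The primary outcomes would be the improvement and/or reestablishment of the function of masticatory muscles and the physiological sleep variables". The Discussion section of the article gives a second wording. There the three therapies "may improve masticatory and oral pharynx muscle modulation, adjusting them to a level close to normality", and the same sentence goes on to link this to less snoring and sleep apnea. Neither place names a primary variable.

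The Statistical analysis section prescribes paired t or Wilcoxon tests before against after therapy, and ANOVA or Mann–Whitney tests between groups. It gives one criterion for all of them: a P value at or below "0.05 will be considered statistically significant". The section on the phases of the electromyography examination says that comparisons between groups and within persons both serve to judge effectiveness.

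The Sample size section states "90% reliability to identify a relevant outcome will be present at the bidirectional α level of 0.05", with 10 subjects per group. Its effect is tied to muscle activity only: "The intervention was considered to result in a minimum effect similar to the EMG activity of the masseter and temporalis muscles in disabled adults".

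**The concern.** When a domain is primary and no variable within it is singled out, any significant member of the domain can be reported as the primary result. Here there are two such domains, three arms, and two kinds of comparison per variable, all at the same threshold. A reader who sees the 0.05 in the sample size would take it as the risk of a false primary claim. Under the stated rules it is the risk for one test among dozens. The sleep domain is also primary, yet the sample size rationale does not cover it.

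**Working it through.** **Inputs from the protocol**

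- Muscles: 4 (right and left masseter, right and left anterior temporalis), from the electromyographical parameters section.
- Conditions: 3 (rest, MVC, MHI), giving 4 × 3 = 12 RMS values. Bite force and mouth opening bring the masticatory count to 14.
- Sleep variables named in the Discussion: at least 5 (desaturation, REM sleep, deep sleep, snoring, sleep apnea). The minimum total is 14 + 5 = 19. Frequency-domain measures, the arousal index and other polysomnography variables would add to it.
- Arms: 3, all active. Subjects: 10 per arm before the dropout allowance.

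**The plan's own figure.** The total is 3 × (10 + 5) = 45, which agrees with the stated recruitment. The 10 per group cannot be reproduced, because no effect size, standard deviation or test is given. Solving back for 90% power at two-sided 0.05 with n = 10 gives d = 1.15 for a paired t test, d = 1.53 for a two-sample t test, or f = 0.69 for a three-group ANOVA. Each of these is for one test.

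**Error rate with independent tests.** With no true change, the chance of at least one false positive in m tests is 1 − 0.95^m.

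- One variable per domain, one test each: 1 − 0.95² = 9.75%
- One variable per domain, tested within each of 3 arms: 1 − 0.95⁶ = 26.5%
- 12 RMS values × 3 arms = 36 tests: 1 − 0.95³⁶ = 84.2%
- 19 variables × 3 arms = 57 tests: 1 − 0.95⁵⁷ = 94.6%
- 19 between-group tests only: 1 − 0.95¹⁹ = 62.3%

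**Allowing for correlation.** The variables are correlated, and the protocol gives no figure, so a range was simulated: change scores equally correlated within an arm, arms independent, n = 10 per arm, no true change.

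| Tests counted | 0 | 0.3 | 0.5 | 0.7 | 0.8 |
|---|---|---|---|---|---|
| 12 RMS values, within 3 arms | 84% | – | 71% | – | 49–50% |
| 19 variables, within 3 arms | 95% | 90% | 82% | 68% | 57% |
| 19 variables, between-group ANOVA only | 62% | 54% | 43% | 31% | – |

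The columns are the assumed correlation. For non-normal data the protocol names the Mann–Whitney test, which compares two groups. Three groups then mean up to three pairwise tests per variable, which the table does not count.

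**The case against.** Four points can be made on the other side.

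**Unseen documents.** The article is condensed, and a full protocol, registry record or SAP may name the primary variable or add an adjustment. Silence on multiplicity alone would therefore not be a finding. But this document itself declares domain-wide primary outcomes and a flat threshold, and that remains open to criticism.

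**Size.** A reader might infer that a false positive primary result is more likely than not. The documents do not support that without conditions. It requires that nothing truly changes, that within-arm tests are pooled over the three therapies, and that correlation is below about 0.8. High correlation is plausible, because the values come from bilateral muscles in one session and share a normaliser. Whether three different therapies form one error family is also debatable. On between-group ANOVA alone the rate falls below one half at a correlation of 0.5. It is still about six times the nominal 5% at 0.7.

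**What counts as primary.** No section lists each polysomnography or frequency-domain measure as a primary test. The counts of 12 and 19 follow from the domain wording and are not an enumerated list. This stands, and it is why a range is given.

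**Abstract against Discussion.** A reader might also infer that the two places disagree on the primary domain, because the Discussion says that "polysomnography will be used to evaluate the other sleep variables and the authors believe that sleep quality will improve". This does not hold. The Discussion's primary-outcome sentence itself extends to reduced snoring and sleep apnea, so the remaining sleep variables can be read as those beyond these two. Both places also treat salivary measures as secondary. The wording is looser in the Discussion, but no domain is demoted.

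**Conclusion.** The point holds in conditional form. The primary outcome is two domains without a named variable, the only decision rule is P ≤ 0.05 for each test, and the 0.05 in the Sample size section is therefore not the error rate of the primary conclusion. If there is no true change, the chance of at least one false positive is about 50% to 84% for the 12 RMS values in three arms (correlation 0.8 to 0), about 57% to 95% for 19 variables in three arms (same range), and about 31% to 62% for ANOVA alone on 19 variables (correlation 0.7 to 0). The floor is instructive: one variable per domain, each tested once, already gives up to 9.75%. The correlations are assumptions, and 19 is a minimum count of the variables named. The need to name primaries does not depend on which figure in these ranges is right.

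**What to change.** Name two primary variables from data already planned.

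- **Muscle:** one summary over the four muscles that the normalisation does not fix in advance, for example un-normalised RMS in μV at MVC, or else bite force. The section on analysis of surface electromyography data divides RMS by the highest MHI or MVC reading, so normalised values at MVC are pushed towards 100% by construction.
- **Sleep:** the apnea/hypopnea index.

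Test each by one three-group comparison of change from baseline, with pairwise contrasts only after a significant global test. Control the two global tests by Holm: the smaller P value at 0.025, then the other at 0.05. If pairwise contrasts are also to carry confirmatory weight, the simplest safe course is to keep each endpoint at 0.025 throughout. Label all other electromyographic, polysomnographic and salivary variables secondary or exploratory and report them with 95% confidence intervals. Use the same two primaries in the Abstract, Discussion and Sample size section.

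The cost is wording and some power. Take the effect implied by 90% power for a paired test at n = 10 (d = 1.15), and treat it as a between-arm difference in change. Two-sample power for one such contrast then falls from about 68% to 56% at 10 per arm, and from 86% to 78% at 15 per arm, when alpha goes from 0.05 to 0.025. Both the step from a within-arm to a between-arm comparison and the smaller alpha lower the power. The d of 1.15 assumes that the original calculation was paired, which the protocol does not say. The stated 90% should therefore be recalculated for the named primary comparisons, with the effect size and standard deviation written out.

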**Trial registration:**

Registro Brasileiro de Ensaios Clínicos, RBR-3qp5np*.* Registered on 20 February 2018.

**Electronic supplementary material:**

The online version of this article (10.1186/s13063-019-3300-0) contains supplementary material, which is available to authorized users.

## Background

The chromosomal alteration caused by trisomy 21, known as Down syndrome (DS), is the main cause of mental impairment and is also related to several psychosocial limitations and comorbidities. Its prevalence in the general population is 1 per 600–800 live births. Nevertheless, if these conditions are well managed, these individuals may reach their full potential regarding mental and physical health, which allows their inclusion in society [1].

This condition is usually accompanied by mental retardation at many levels, cardiovascular disease, thyroid dysfunction, upper airway obstruction, respiratory breathing disorders, reduced size of maxillary and mandibular bones, muscular hypotonia, breathing through the mouth, risk for aspiration pneumonia, and low immunity, among other features [2–4].

Considering that muscle hypotonia is one of the main characteristics in individuals with DS that can affect any muscle in the body, the loss or reduction of upper airway (UA) muscle tone, including the oropharynx, velopharynx, hypopharynx, and tongue base muscles, may lead to partial/total obstruction causing obstructive sleep apnea (OSA) [5, 6].

In addition, the diminished activity of the genioglossus and other dilator muscles combined with an altered UA anatomy are probably the main cause of obstructive events [7–10]. This disease is a growing public health issue and is associated with a high risk of morbidity and mortality [4].

The genioglossus, a representative dilator muscle of the upper airways, plays an important role in the pathophysiology of OSA. In apneic individuals, a reduction in the activity of several muscles of the UA is observed. To compensate for this, some dilator muscles, along with the genioglossus, may increase activity in response to an increased negative pressure. When the dilator muscles reflex is not sufficient to compensate the negative pressure, the upper airway may collapse. This fact was demonstrated by Jordan et al. [7], who observed that when apneic individuals spontaneously overcame their tendency for UA collapse and had stable breathing during sleep, the genioglossus muscle was more active than during respiratory events, demonstrating that augmentation of genioglossus muscle tone is associated with spontaneous periods of stable flow-limited breathing in apneic individuals.

An animal model study and an investigation with healthy individuals have shown that greater respiratory resistance induces increased muscle activity of the orofacial muscles, bringing the tongue forward and opening the mouth for better respiration [9, 10], but in OSA individuals the amount of muscle reflex may be not enough to prevent the disease. The exact mechanism of OSA is not totally clarified and finding new pathways to sufficiently increase the activity of upper airway muscle is necessary, including in persons with disability.

The prevalence of obstructive sleep apnea (OSA) in adults with DS is still unknown, but in children the prevalence is around 66% [5]. Adults with DS will commonly present signs of OSA, hypoxemia, and sleep fragmentation [6]. Symptoms of OSA include snoring, excessive daytime somnolence, fatigue, nonrestorative sleep, memory lapses, cognitive impairment, and mood alteration. If OSA remains nontreated, various comorbidities may take place, such as hypertension, stroke, insulin resistance, metabolic alteration, and depression/anxiety.

Studies have demonstrated satisfactory results through oropharyngeal exercises in adult patients with no disability. However, a portion of people with disability has compromised cognition, which would prevent this population performing the oropharyngeal therapy correctly [11, 12]. Thus, new therapies are necessary in order to allow an improvement in upper airway muscles in this population.

There are few research studies correlating the masticatory muscle functions and sleep disorders in adult patients with DS. Thus, previous studies have suggested that new therapeutic approaches are promising options to improve masticatory muscle function and to treat sleep disorders, including sleep bruxism and OSA. These investigations have demonstrated satisfactory results in patients with disabilities who presented concomitant unbalanced masseter and temporalis muscle patterns, sleep bruxism, and OSA [13–15].

One of these studies used surface electromyography (sEMG) to evaluate pre and post treatment of masticatory muscle functions of severe sleep bruxism with mechanical stimulus in a child with cerebral palsy. The results showed a reduction of sleep bruxism and electrical activity balance in the masticatory muscles after mechanical stimulus with the mastication instrument Hiperboloide® [13]. It is important to provide the brief information that this mastication instrument was also named hyperbola, hiperbolide, or hyperboloid in different previous studies, but all are the same device [13, 16]. In other work, Giannasi et al. [14] demonstrated that it is possible to achieve electrical activity balance in the masticatory muscles and a reduction in OSA severity using neuromuscular electrical stimulation (NMES) therapy through sEMG and polysomnography (PSG). The authors showed a statistically significant reduction in snoring and respiratory events after the treatment with NMES in adult cerebral palsy. Also, parents have reported a visible reduction of chewing and drooling in daily routine function [8]. The sustained hypothesis for this positive result is that the neuroelectrical stimulus has reverberated on all muscular chains from activation of the masseter and temporalis muscles, and indirectly improved the oropharyngeal, velopharyngeal, and tongue base tonus, which also resulted in a decrease of respiratory events.

NMES has been used for maintenance of muscle mass, strength during long periods of immobilization, selective muscle retraining, and muscle strength. It is not only used to treat spasticity [17]. So, it may also be used to treat hypotonia, as seen in a recent study by Pinheiro et al. [18] that showed positive results in the treatment of weakness muscle with NMES in DS patients. The authors found significant differences in the muscle behavior during breathing, swallowing, and mastication function, pre and post treatment with NMES, applied on the masseter [10]. Based on these outcomes, they inferred that muscle fibers can modify their physiologic and biochemical characteristics according to the stimulus to which they are submitted. Such adaptive capacity involving several components of the fiber corresponds to muscular plasticity. Fraga et al. [19] stated that the mechanism of muscular contraction may occur due to a controlled and coordinated voluntary command by the brain, or due to an involuntary contraction induced by an external electrical stimulus. Abdel-Moty et al. [20] and Tong et al. [21] also showed positive results with the use of NMES to treat hypotonia and to promote change in the muscle fiber composition. Thus, the therapeutic options (i.e. mechanical and electrical stimulation) and the relationship between the masticatory muscles and the respiratory function are still not well studied and need to be better understood and clarified.

Another usual option to treat snoring, OSA, and associated symptoms is the mandibular advancement oral appliance (OA_m_). The OA_m_ is a therapy to manage OSA and refers to the mandibular advancement. Thus, the OA_m_ function is to protrude and to stabilize the mandible in order to maintain the patency of the upper airway (UA) during sleep. The action mechanism of the OA_m_ aims to increase the volume and to reduce the collapsibility of the UA with the mandibular advancement. The OA_m_ will protrude the mandible and the tongue, since the genioglossus that is one of the tongue’s major muscles is attached to the lingual surface of the anterior mandibular arch. The increase in the upper airway dimension occurs especially in the velopharyngeal area, which is greater than in the oropharyngeal and hypopharyngeal sites. This is likely a consequence of stretching the soft tissue connecting the soft palate, lateral pharynx, tongue, and palatopharyngeal arches. All of this upper airway alteration will promote the reduction and/or elimination of snoring and other respiratory events, as well as associated symptoms. In patients with no disability, the OA_m_ is a safe and effective treatment for OSA, with positive results [22]. Also, patients report that after OA_m_ usage they observed an improvement in word spelling in the daily clinic [23]. Nevertheless, there are few studies in the current literature using the OA_m_ in adults with DS to treat snoring and obstructive sleep apnea based on caregiver observations. Yoshida [24] showed a great decrease of respiratory events in patients with cerebral palsy and DS treated with the OA_m_, and stated that this a promising option for this population who usually refuse the use of continuous positive airway pressure (CPAP).

In addition to hypotonia and respiratory sleep disorders, muscle weakness, and slowness in information processing and motor response and in sensory alterations, usually linked to DS, may impair the capacity of these individuals to keep an adequate muscle balance. Consequently, the movements became difficult, slow, and disorganized, also altering swallowing and raising the risk of aspiration pneumonia, thus resulting in feelings of stress, anxiety, and frustration from the usual demands of daily tasks. Therefore, the effects of stress and/or poor sleep quality may trigger an increase in cardiovascular tone, alter heart rate variability, and generate an imbalance of microorganisms in the oral cavity [25, 26]. In addition, analysis of the salivary parameters is a valuable tool to evaluate susceptibility to stress and the lack of balance of microorganisms present in the saliva [27–30].

